#### Data management

Patient screening and recruitment will be collected on encrypted Excel spreadsheets for each physiotherapy team, saved on the health service password-protected drive and shared securely with the research team. All paper-based participant data will be coded with a unique study ID number and will be entered into a password-protected REDCap database [59, 60] with a license held by The University of Sydney. Access to this database will only include the Chief Investigator and required members of the research team.

#### Quantitative analysis

The planned quantitative analysis has been designed by CS and LH, overseen initially by a local statistician. The analysis will be conducted by LH and CS using STATA statistical software. Primary analyses will be pre-planned and conducted while masked to group allocation. To account for correlation among individuals within clusters, all statistical models will use a generalised estimating equations (GEE) approach with an exchangeable correlation structure.

##### Patient-level effectiveness outcomes

The primary analysis will evaluate the effect of the multi-faceted implementation strategy to train, support and facilitate physiotherapists to deliver brief physical activity counselling as part of their routine care [targeted at the cluster level] on primary and secondary effectiveness outcomes. The main (intention-to-treat (ITT)) dataset analysed will be constituted of all patients recruited into the study irrespective of what amount of physical activity counselling they received from their treating physiotherapist. For the continuous outcomes, multiple linear regression will be used with a group (immediate-implementation vs. waitlist control) as the primary independent variable and baseline scores as a covariate. Binary logistic regression will be used to compare groups on dichotomous outcome measures with the group as the primary independent variable.

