### Recruitment and allocation

#### Clinical teams

Thirty clinical teams will be recruited as clusters and randomised to either the immediate-implementation group (who will receive the multi-faceted implementation strategy immediately) or the waitlist control group (who will receive an updated version of the multi-faceted implementation strategy at the end of the trial). Eligible clinical teams will be identified by the Chief Investigator (LH) in collaboration with the District Physiotherapy Director (MJ) and the Physiotherapy Head of Department at each hospital site. The Chief Investigator will present the study protocol at department meetings and the Head of Department will then liaise with their staff regarding interest and eligibility to participate. Physiotherapists within eligible teams who agree to participate will be consented prior to the team being randomised. The randomisation schedule will be generated and managed by the Clinical Trials Centre at The University of Sydney who are not involved in the recruitment of clusters to ensure concealed allocation. The randomisation schedule includes minimisation based on the average number of occasions of service delivered by each clinical team (high dose vs. low dose i.e. equal to or above vs. below the median number of occasions of service) [24]. When there is a team(s) to randomise, the Chief Investigator will email the Clinical Trials Centre who will complete the randomisation and email the team allocation within 24 h.

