### Data collection methods and outcome measures

As a hybrid type II study [29], patient-level effectiveness and implementation outcomes will be measured. All effectiveness outcomes (excluding device-measured physical activity and impressions of physiotherapy) as well as demographic information and co-morbidities will be assessed at baseline to enable a description of the patient-participant’s baseline characteristics and to obtain values to enter as covariates in the models comparing groups at follow-up. At the time of consent, the treating physiotherapist will provide the participant with a copy of the paper-based survey. This will be completed independently by participants or assisted by study staff over the telephone who are blinded to physiotherapy team allocation. At 6 months post-baseline, follow-up paper-based surveys will be mailed to participants and followed up by blinded research staff if surveys are not returned by mail.

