##### Implementation outcomes

Implementation outcomes are measured both with respect to the delivery of brief physical activity counselling within routine physiotherapy care and delivery of the multi-faceted implementation strategy to support and train physiotherapists. Some of these are measured for both groups with between-group statistical comparisons conducted, and others are measured only for the immediate-implementation group and the statistics will be presented descriptively (see Table 3). For the continuous outcomes measured for both groups evaluating the delivery of brief physical activity counselling (reach, dose delivered and fidelity), multiple linear regression will be used with the group as the primary independent variable. All other implementation outcomes will be descriptively presented.

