#### Exploratory subgroup analysis

The study is not powered to detect between-group differences for subgroup analysis. However, exploratory and pre-specified subgroup analyses will be undertaken on the co-primary outcomes to help understand if these variables are likely to impact on the outcomes and should be included in future implementation trial designs. All subgroups will be defined by data collected prior to randomisation. Subgroup analysis will be conducted for patient gender (male versus female), age (entered as continuous and categorical (above and below median age) covariates), language spoken at home (English versus non-English), recruited from inpatient vs. outpatient physiotherapy team and recruited from high-dose vs. low-dose physiotherapy team.

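### Teams are minimised on occasions of service, but the main between-group models leave that factor out; separately, the baseline-score rule cannot be applied to step count.

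*Protocol article*

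**What the plan says.** Recruitment and allocation, Clinical teams: "The randomisation schedule includes minimisation based on the average number of occasions of service delivered by each clinical team", with teams classed as high or low dose by a split at the median.

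Quantitative analysis: "all statistical models will use a generalised estimating equations (GEE) approach with an exchangeable correlation structure". Under Patient-level effectiveness outcomes, the model for measures on a continuous scale is given as follows: "multiple linear regression will be used with a group (immediate-implementation vs. waitlist control) as the primary independent variable and baseline scores as a covariate". The model for binary measures is given thus: "Binary logistic regression will be used to compare groups on dichotomous outcome measures with the group as the primary independent variable". Under Implementation outcomes, the model that covers fidelity, dose delivered and reach is given in these terms: "multiple linear regression will be used with the group as the primary independent variable. All other implementation outcomes will be descriptively presented".

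The allocation factor appears once more, in the Exploratory subgroup analysis of the co-primary outcomes: "recruited from high-dose vs. low-dose physiotherapy team".

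On baseline measurement, Data collection methods and outcome measures begins with "All effectiveness outcomes (excluding device-measured physical activity and impressions of physiotherapy" and says that the outcomes not excluded there are assessed at baseline, partly to supply covariates. Average steps per day is listed among the secondary effectiveness outcomes and is continuous.

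**The concern.** Minimisation makes the arms alike on the chosen factor, so any part of the outcome that the factor explains nearly cancels from the difference between arms. A model without the factor does not know this. It counts the factor's contribution as unexplained variation between teams and reports a standard error larger than the true sampling error of the contrast. The interval is then too wide and the test runs below its nominal level. With 30 teams and a planned-activity comparison sized with no margin, that precision is worth having.

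The subgroup analysis does not repair this, because it leaves the main estimate and its standard error unchanged.

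A second, separate matter is that the baseline-score rule covers the continuous outcomes without exception, while step count is one of them and is not measured at baseline. As written, the rule has nothing to enter for it.

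**Working it through.** **Inputs from the Sample size section:** difference 1.5 h/week, SD 4.4, two-sided alpha 0.025 (sidedness is assumed), 15 teams per arm, 10 patients per team, ICC 0.05, and a baseline term of 0.6, read as a correlation.

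**Input not in the documents:** the share R² of between-team variance explained by the high/low factor. It is treated as a range.

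**1. Reproduce the plan's figure.**
- Design effect: 1 + 9 × 0.05 = 1.45.
- Residual variance factor: 1 − 0.6² = 0.64, so the residual SD is 4.4 × 0.8 = 3.52.
- Two-means formula: 105 per arm; 105 × 1.45 = 152 per arm, about 305 in all against the stated 300.
- Standard error at 300: √(2 × 4.4² × 0.64 × 1.45 / 150) = 0.489 h.
- Power: 79.5% by normal approximation, 75.3% with a t test on 28 df.

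The stated sample size therefore reproduces. Without the 0.6 term the power would be 58.3%.

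**2. Effect of adding the factor.** With balance on the factor, the ratio of adjusted to unadjusted standard error is

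√{[ICC(1 − R²) + (1 − ICC)/m] / [ICC + (1 − ICC)/m]}.

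With ICC 0.05 and m = 10 the denominator is 0.05 + 0.095 = 0.145. For R² = 0.50 the numerator is 0.025 + 0.095 = 0.120, and √(0.120/0.145) = 0.910.

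**3. Simulation.** Thirty teams were minimised on one binary factor and analysed on team means, with and without the factor, by t tests at two-sided 0.025. Approximate results for planned activity:

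| R² | SE reduction | Test level without factor (nominal 2.5%) | Power for 1.5 h, without → with |
|---|---|---|---|
| 0 | 0% | 2.5% | 75 → 75% |
| 10% | 2% | 2.2% | 75 → 76% |
| 25% | 4% | 1.8% | 76 → 79% |
| 50% | 9% | 1.5% | 77 → 83% |
| 75% | 15% | 1.0% | 78 → 87% |

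In hours, the unadjusted standard error is about 0.49, against 0.464, 0.442 and 0.419 adjusted at R² of 25, 50 and 75%. The formula agrees to within about one percentage point. With the factor in the model, the t test holds its level at about 2.5%. At R² = 0 the cost is at most about 0.5 power points.

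**4. Sensitivity to ICC.** At ICC 0.10 and R² = 50% the ratio is √(0.14/0.19) = 0.858, and power moves from about 63 to 77%.

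**5. Sensitivity to the variance estimator.** The article specifies GEE but no variance estimator. With an uncorrected sandwich standard error and a z test, the level without the factor is 3.8, 3.3, 2.6 and 1.9% at R² of 0, 25, 50 and 75%. With the factor it is about 4.2 to 4.3% throughout.

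**6. Reach.** On the stated inputs (35% against 60%, 150/1.45 ≈ 103 effective patients per arm) power is about 92%. The effect of the factor on reach was not computed.

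**7. Step count.** No arithmetic applies. One section excludes device-measured activity from baseline; the other requires a baseline score for continuous outcomes and makes no exception.

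**The case against.** **The loss is conditional.** A reader might infer that the intervals for both co-primary outcomes are certain to be too wide. The documents do not support that: they give no figure for how well a median split on occasions of service predicts planned activity or reach. At R² = 10% the gain is about 2%, and at zero there is none. This stands and limits the claim.

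**The conservative direction depends on the standard error.** The below-nominal levels come from t tests on team means. Under an uncorrected sandwich z test the unadjusted model can run above 2.5%, and adding the factor alone takes it to about 4%. This also stands, and it is why the fix couples the covariate with a small-sample correction.

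**Reach and the logistic models.** It is tempting to call both co-primaries short of power, but reach has about 92% on the protocol's inputs. In a logistic model a prognostic covariate does not simply shrink the standard error of the log odds ratio; it changes the odds ratio from marginal to conditional. The precision argument is therefore shown only for planned activity.

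**Step count.** It might be inferred that precision is lost here too. It is not, since no baseline step count exists to be used. One can also read the two sections together so that the covariate applies only where a baseline exists. That is a sensible reading, but the model sentence does not say it.

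**Scope.** A full covariate list is commonly left to the analysis plan, and calling group the primary independent variable does not rule out others. This carries some weight. However, the article names both the allocation factor and the covariates, and the two do not match, so the point concerns a stated model rather than an omitted detail.

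**Setting.** The exploratory analysis also lists "recruited from inpatient vs. outpatient physiotherapy team and recruited from high-dose vs. low-dose physiotherapy team". Adjusting for inpatient or outpatient setting is a matter of preference: it is not an allocation factor, and no calculation here supports it.

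**Conclusion.** The point holds in a limited form. The main between-group models, as written, omit the factor on which teams were balanced. If that factor is prognostic, this gives away precision that the design has already secured. For planned activity at the planning ICC, the adjusted standard error is about 2 to 15% smaller as R² runs from 10 to 75%. The power gain is about 1 point at 10%, 3 at 25%, 6 at 50% and 9 at 75%.

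These figures rest on an assumed range for R², equal team sizes of 10, near-exact balance, and t tests on team means in place of the GEE. The omission does not bias the estimate through imbalance on this factor, and it does not call the sample size into question. It is a low-cost improvement worth making, not a threat to validity.

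The step-count conflict is a separate, certain but minor wording defect with no consequence for precision.

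**What to change.** 1. Add the high/low occasions-of-service factor as a pre-specified covariate in the main between-group models for planned activity, for reach, and for the other outcomes compared between arms.
2. In the same sentence, specify a small-sample correction for the GEE standard errors. Adding the covariate without it would leave an uncorrected sandwich z test at about 4% against a nominal 2.5%.
3. For logistic models, state that the odds ratio is conditional on the factor.
4. State a separate rule for step count, for example no baseline covariate, or baseline IPEQ total as a proxy.

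The factor is known before randomisation, so no new data are needed and the sample size is unchanged. The price is one degree of freedom (28 to 27 on team means), at most about 0.5 power points if the factor turns out not to be prognostic. Adjustment for inpatient or outpatient setting is optional.

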##### Implementation outcomes

Implementation outcomes are measured both with respect to the delivery of brief physical activity counselling within routine physiotherapy care and delivery of the multi-faceted implementation strategy to support and train physiotherapists. Some of these are measured for both groups with between-group statistical comparisons conducted, and others are measured only for the immediate-implementation group and the statistics will be presented descriptively (see Table 3). For the continuous outcomes measured for both groups evaluating the delivery of brief physical activity counselling (reach, dose delivered and fidelity), multiple linear regression will be used with the group as the primary independent variable. All other implementation outcomes will be descriptively presented.

#### Exploratory subgroup analysis

The study is not powered to detect between-group differences for subgroup analysis. However, exploratory and pre-specified subgroup analyses will be undertaken on the co-primary outcomes to help understand if these variables are likely to impact on the outcomes and should be included in future implementation trial designs. All subgroups will be defined by data collected prior to randomisation. Subgroup analysis will be conducted for patient gender (male versus female), age (entered as continuous and categorical (above and below median age) covariates), language spoken at home (English versus non-English), recruited from inpatient vs. outpatient physiotherapy team and recruited from high-dose vs. low-dose physiotherapy team.

#### Implementation determinants

Quantitative and qualitative data will be synthesised following mixed methods approaches [61] to understand implementation determinants. Change in physiotherapists’ self-reported Capabilities, Opportunities and Motivations to deliver physical activity counselling after receiving the implementation strategies will be presented as mean (SD) for each item. Univariate correlations will explore change in Capabilities, Opportunities and Motivations and Engagement (see Fig. 2) with the reach, dose delivered and fidelity of physical activity counselling provided to help understand key elements of implementation strategies for changing the behaviour of physiotherapists.

Audio-recordings of each post-implementation focus group or interview will be transcribed verbatim and imported into NVivo 12 (QSR International, Australia). A thematic analysis will be conducted to explore determinants of implementation outcomes. The coding frame will be informed by the CFIR [42] and Normalization Process Theory, supplemented by inductive coding to capture additional relevant information.

#### Economic analysis

The economic evaluation will be conducted by MP and overseen by KH and AP and will include a cost-effectiveness and cost-utility analysis and take a health care payer perspective, with the time horizon limited to the trial duration. Costs will include program delivery costs (including staff and equipment costs) and health service utilisation costs. The brief physical activity intervention delivery costs (physiotherapy staff hours and equipment costs) will be estimated using trial-specific data and costed using appropriate wage rates and on-costs. The multi-faceted implementation strategy preparation and delivery costs (research staff hours and resource development costs) will be estimated using trial-specific data and costed using appropriate wage rates and on-costs. Using the mean costs and the mean health outcomes in each trial arm, the incremental cost per (1) additional person achieving a clinically meaningful increase in physical activity based on the IPEQ, (2) additional person with any improvement in quality of life (from PROMIS-29) and (3) quality-adjusted life-year (QALY) gained (from EQ5D-5L) in the intervention group compared with the control group will be calculated. Bootstrapping will be used to estimate a distribution around costs and health outcomes and to calculate the confidence intervals around the incremental cost-effectiveness ratios (ICER). Results will be plotted on a cost-effectiveness plane. A range of additional sensitivity analysis will be conducted to determine the impact on the ICER of various assumptions within the economic evaluation, such as the efficacy or fidelity of the intervention in the longer term, strategies for handling missing data, use of alternative methods for QALY estimation, or different cost scenarios for alternative implementation strategies. A specific scenario analysis will also be conducted to evaluate the cost-effectiveness of multi-faceted implementation strategies and sustainability strategies being conducted by staff employed through the local health district rather than the research team.

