Physiotherapists are ideally placed to deliver physical activity counselling within their routine healthcare interactions. Physiotherapists can effectively deliver physical activity counselling [22], and patients see them as trustworthy physical activity messengers [23]. Physiotherapists have expertise in exercise prescription for a range of different health conditions and typically see patients on multiple occasions over an extended period which is ideal for supporting behaviour change [24]. Physiotherapists surveyed around the world agree that the promotion of physical activity should be part of their clinical role [25–28]. However, current efforts to put this into practice have been sub-optimal with only 36 to 54% of physiotherapists surveyed in different countries reporting they promote physical activity beyond therapeutic exercise to 10 or more patients per month [25, 26, 28]. Physiotherapists report similar barriers to implementation as other healthcare professionals [25–28].

The Brief Physical Activity Counselling by Physiotherapists (BEHAVIOUR) cluster randomised controlled trial will aim to address this evidence-practice gap by delivering a multi-faceted implementation strategy to teams of hospital-based physiotherapists to support them to implement brief physical activity counselling into routine care, which will, in turn, increase physical activity levels of patients receiving physiotherapy. A cluster design has been chosen to avoid the risk of contamination among individual physiotherapists working together within clinical teams. Although there is strong evidence for brief physical activity counselling in healthcare, few studies have been conducted with physiotherapists working in a public hospital setting, and few studies have been conducted in lower socioeconomic areas with patients from culturally and linguistically diverse backgrounds. Consequently, we cannot be certain that the implementation of brief physical activity counselling in this setting will increase the physical activity levels of the population of interest. Therefore, we will conduct an effectiveness-implementation hybrid type II study [29] with equal interest in implementation and effectiveness outcomes. This design is particularly suited to situations such as ours where there is good buy-in in the clinical setting, but intervention effectiveness is not yet known for this particular setting and population [30].

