We hypothesise that physiotherapists who receive the multi-faceted implementation strategy will be better able and more motivated to incorporate brief physical activity counselling into routine care (measured by reach, dose delivered and fidelity of the physical activity counselling) than physiotherapists who have not received the multi-faceted implementation strategy. In turn, we hypothesise that patients who receive their physiotherapy care from a physiotherapist who has participated in the multi-faceted implementation strategy will be more likely to achieve greater amounts of planned physical activity at 6-month follow-up than patients who receive physiotherapy care from a physiotherapist who has not yet participated in the multi-faceted implementation strategy. We also hypothesise that the multi-faceted implementation strategy will be a cost-effective way to achieve practice change and greater physical activity among patients.

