### Data analysis and management

#### Sample size

The sample size calculation was undertaken in STATA 14.2 using the “clustersampsi” command. Recruitment of 300 patients undergoing physiotherapy is sufficient to detect a 1.5-h between-group difference in the self-reported time spent in planned physical activity per week, estimated at 3 h/week (SD 4.4 hours/week) (waitlist control group) to 4.5 h/week (immediate-implementation group) (a between-group difference found to be achievable in our previous study [58]). All calculations used 80% power, alpha = 0.025 (to account for co-primary outcomes), 15 clusters per arm, average cluster sizes of 10, baseline-covariance 0.6 and intracluster correlation 0.05. This sample size will also be sufficient to detect an absolute 25% difference in the proportion of eligible patients receiving brief physical activity counselling within routine physiotherapy care (primary implementation outcome (reach), 35% in the waitlist control group and 60% in the immediate-implementation group).

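### The only interval the economic plan fixes is a bootstrap interval around the ICER, which cannot be read when replicates cross zero effect; net benefit from the same replicates can

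*Protocol article*

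**What the plan says.** The Background section ends its hypotheses with an economic one: "We also hypothesise that the multi-faceted implementation strategy will be a cost-effective way to achieve practice change and greater physical activity among patients". The Economic analysis section defines three ratios: cost per additional person with a clinically meaningful IPEQ increase, per additional person with any PROMIS-29 improvement, and per QALY gained. On uncertainty it says "Bootstrapping will be used to estimate a distribution around costs and health outcomes" and that the bootstrap will also be used to "calculate the confidence intervals around the incremental cost-effectiveness ratios (ICER"). It then adds: "Results will be plotted on a cost-effectiveness plane". The analysis is to be run "with the time horizon limited to the trial duration".

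The section names no willingness-to-pay value, no decision rule for the hypothesis and no particular construction for the bootstrap interval.

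**The concern.** Cost-effectiveness is about whether the value of the extra effect exceeds the extra cost. The ratio of cost difference to effect difference tracks that only while the effect difference keeps one sign. A negative ratio arises both when the strategy dominates and when it is dominated. As the effect difference passes through zero, the ratio jumps between very large positive and very large negative values. Sorting bootstrap ratios and cutting off the tails then does not sort the replicates by value for money.

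The setting makes this likely to matter. The Background section says "we cannot be certain that the implementation of brief physical activity counselling in this setting will increase the physical activity levels", so an effect near zero is an outcome the investigators themselves allow for. Patients are followed for 6 months, so QALY differences are likely to be small. Two of the three effect measures are dichotomised, which gives up precision relative to the continuous primary outcome. What is at stake is whether the interval reported for a stated hypothesis, in a trial meant to inform policy makers, can be interpreted.

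**Working it through.** **1. The plan's own figure.** The economic section contains no numbers, so the check starts from the Sample size section: "Recruitment of 300 patients undergoing physiotherapy is sufficient to detect a 1.5-h between-group difference". Its inputs are SD 4.4 h/week, 15 clusters of 10 per arm, ICC 0.05, baseline value 0.6 (labelled a covariance, taken here as a correlation) and alpha 0.025 (taken as two-sided).
- Design effect = 1 + (10 − 1) × 0.05 = 1.45.
- Adjusted SD = 4.4 × √(1 − 0.6²) = 3.52.
- SE = 3.52 × √(2 × 1.45/150) = 0.489, and 1.5/0.489 = 3.06.
- Power = 79.5%. The stated 80% with 300 patients reproduces.

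**2. The ratio does not separate opposite results.** Take an assumed value of 50,000 per QALY; the protocol gives none. Net benefit = 50,000 × effect difference − cost difference.

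| Cost difference | Effect difference (QALY) | ICER | Net benefit |
|---|---|---|---|
| −500 | +0.01 | −50,000 | +1,000 |
| +500 | −0.01 | −50,000 | −1,000 |

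**3. How often replicates cross zero effect: IPEQ-responder ratio.** The inputs are those of step 1. Further assumptions are normal change scores, a mean change of zero in the control arm and 1.5 h in the intervention arm, the same ICC for the binary outcome, and a cut-off between 0 and 1.5 h, since none is stated.
- SD of change = 4.4 × √(2 × (1 − 0.6)) = 3.94.
- Cut-off 0: control proportion 0.500; intervention proportion Φ(1.5/3.94) = 0.649; difference 0.149.
- SE = √[(0.500 × 0.500 + 0.649 × 0.351) × 1.45/150] = 0.068.
- z = 0.149/0.068 ≈ 2.18. Over cut-offs of 0 to 1.5 h, z is 2.18 to 2.20.
- Crossing means at least 2.5% of replicates on each side of zero effect, that is, an estimated |z| below 1.96. At the full planned effect, Φ(1.96 − 2.18) − Φ(−1.96 − 2.18) ≈ 0.41.
- Under no effect the probability is 0.95 by construction.

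This step needs no cost assumption.

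**4. What the interval looks like at zero QALY effect.** With a true effect of 0, extra cost of 300, QALY SD of 0.05 to 0.15 and cost SD of 3,000 to 8,000 (all assumed), the 95% percentile interval of the ratio runs from about −310,000 to +319,000 at its narrowest and about −2.1 to +2.1 million at its widest. Draws fall in all four quadrants. The share of ratios below 50,000 is 0.59 to 0.85, while the share with positive net benefit is 0.29 to 0.42.

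**5. Could the interval look favourable for a worse, dearer strategy?** Assumed inputs: QALY SD 0.10, extra cost 500, cost SD 2,000 to 10,000, value 50,000 per QALY. The SE of the QALY difference is 0.10 × √(2 × 1.45/150) = 0.0139. Replicates cross zero effect in about 70% of simulated trials at a true gain of 0.02. The upper ICER limit falls below 50,000 in about 1 to 7% of trials at a true loss of 0.005, and in 8 to 62% at a loss of 0.02 to 0.03. At those larger losses, the lower limit of net benefit exceeds zero in at most 0.3%.

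**The case against.** The strongest reply is that the plan already contains the safeguard. It bootstraps costs and outcomes jointly, reports mean costs and outcomes by arm, and plots the plane. A dominated strategy would be seen there: nearly all of the simulated trials with a misleadingly low upper limit had a point estimate that was itself worse and dearer (0.601 of 0.621 at a 0.03 loss with cost SD 2,000). This stands as mitigation. The plane is a display, however, and supplies no interval or probability to replace the one the plan specifies.

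Second, percentile limits are an assumption. Replicates can be ordered by angle on the plane, or the interval withheld when they cross zero. That is fair, and the point is confined to percentile-type intervals; the text does not commit to any alternative.

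Third, the large figures in step 5 need an unlikely harm. With EQ5D-5L at baseline and 6 months only, equal baselines and linear interpolation, the QALY difference is 0.5 × 0.5 = 0.25 times the 6-month utility difference. A loss of 0.02 to 0.03 therefore needs a utility harm of 0.08 to 0.12 from counselling the protocol expects to take under 5 minutes. This also stands, and the conclusion does not rest on those figures.

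Fourth, at the planned effect about 59% of trials do not cross zero, and the 95% under no effect is simply the coverage of a 95% interval. Both are true; 41% is still a frequent failure in the case most favourable to the plan.

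Finally, an article may leave net benefit and acceptability curves to a fuller economic plan. Their absence is not the finding. The finding is that the method the article does state is one that breaks down here.

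**Conclusion.** The point holds in a limited form. The one interval specified for the cost-effectiveness hypothesis cannot be interpreted, if built from percentiles, whenever replicates cross zero effect. For the IPEQ-responder ratio that is about 41% of trials at the full planned effect and about 95% under no effect, given 0.6 as a correlation, normality and cut-offs of 0 to 1.5 h.

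Two stronger readings are not supported. A reader might infer that the hypothesis will be accepted or rejected on the ICER interval; the protocol states no such rule and no threshold, so a limit falling below a threshold is a possible misreading rather than a planned decision. A reader might also infer that a harmful strategy would often look cost-effective; that frequency depends wholly on assumed QALY and cost inputs, is about 1 to 7% at a 0.005 QALY loss, and is higher only at larger assumed losses.

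The effect is confined to a secondary economic question. The co-primary analyses are untouched.

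**What to change.** In the Economic analysis section, make incremental net benefit the inferential summary. From the same bootstrap replicates, report it with a 95% interval and a cost-effectiveness acceptability curve over a willingness-to-pay range stated before unmasking. For the IPEQ and PROMIS-29 responder outcomes, state a range only, because the protocol offers no basis for a single value. Report each ICER as a point estimate with the share of replicates in each quadrant of the planned plane, and give an ICER interval only when the replicates do not cross zero effect.

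This changes analysis wording only, with no new data and no new resampling. The cost is having to state the willingness-to-pay range in advance, including for the two non-QALY outcomes.
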